### Sample size {14}

Sample size estimation uses a completely random design to compare multiple sample means. The target sample size was estimated on PR sperm (as the primary outcome of this trial) using the PASS 2021 version 21.0.3 (NCSS, LLC, Kaysville, UT, USA). The number of samples considering the type I error *α* = 0.05 and the type II error *β* = 0.20 with 80% test power. According to a previous study [23], and a retrospective analysis of our data center in the past 2 years, changes in PR sperm mean value in the surgical observation group was 12.05, and the standard deviation was 3.96; changes in PR sperm mean value in the surgical control group was 6.56, and the standard deviation was 8.90; changes of PR sperm mean value in the non-surgical observation group was 4.15, and the standard deviation was 8.68; changes of PR sperm mean value in the non-surgical control group was 1.42, and the standard deviation was 7.60. After calculation, the sample size required for each group was 16 people. To reduce error, we slightly expanded the target sample size and estimated a dropout rate of 20%. The sample size will be practically 20 patients per group, and we will consider a total of 80.

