## Statistical methods

### Statistical methods for primary and secondary outcomes {20a}

Data analysis will be performed using IBM SPSS Statistics for Windows, version 24 (IBM Corp., Armonk, NY, USA). Compliance of variables with normal distribution will be analyzed by the Shapiro-Wilk test and homogeneity of variance by Levene’s test. Continuous variables will be expressed as mean with standard deviation (mean ± SD) or median (25 to 75%). Categorical variables will be expressed as numbers with percentages. Continuous data that are normally distributed and homogeneous in variance will be analyzed with one-way analysis of variance, and if the result is statistically significant, multiple comparisons will be performed with Bonferroni correction. Continuous data that do not obey normal distribution or have unequal variance will be analyzed with the Kruskal-Wallis test, if the result is statistically significant, then the Wilcoxon signed-rank test, with a Holm-Bonferroni method correction for multiple comparisons. Within groups before and after the intervention will be analyzed by paired-samples *t*-test for normally distributed variables and Wilcoxon signed-rank test for non-normally distributed variables. Categorical data will be analyzed using Pearson’s chi-square test or Fisher’s exact test. The level of significance will be set to *p* < 0.05.

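### Pre-tests choose the primary test, and unequal variance leads to Kruskal-Wallis, which neither corrects for it nor estimates the mean difference the trial was sized on

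*Protocol article*

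**What the plan says.** All references are to the protocol article.

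The section on statistical methods for primary and secondary outcomes {20a} sets out a two-stage rule:

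- Pre-tests: "Compliance of variables with normal distribution will be analyzed by the Shapiro-Wilk test and homogeneity of variance by Levene’s test".
- If both are satisfied: "Continuous data that are normally distributed and homogeneous in variance will be analyzed with one-way analysis of variance", followed by Bonferroni-corrected comparisons if the overall test is significant.
- Otherwise: "Continuous data that do not obey normal distribution or have unequal variance will be analyzed with the Kruskal-Wallis test".

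No method for comparing means under unequal variances is named.

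The sample size section {14} plans a comparison of several means and gives these assumptions for the primary outcome, change in PR:

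- Surgical, alpha-lipoic acid (ALA): "changes in PR sperm mean value in the surgical observation group was 12.05, and the standard deviation was 3.96"
- Surgical, vitamin E: "changes in PR sperm mean value in the surgical control group was 6.56, and the standard deviation was 8.90"
- Non-surgical, ALA: "changes of PR sperm mean value in the non-surgical observation group was 4.15, and the standard deviation was 8.68"
- Non-surgical, vitamin E: "changes of PR sperm mean value in the non-surgical control group was 1.42, and the standard deviation was 7.60"

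**The concern.** Three things do not fit together.

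1. **The remedy does not match the problem.** The null hypothesis of Kruskal-Wallis is that all groups share one distribution. When spreads differ, it is not a clean test of means or of medians. It also returns no difference in PR points, which is the scale on which the trial was sized.
2. **The data choose the test.** Whether the primary result is a comparison of means or of ranks depends on preliminary p-values from the same outcome data.
3. **The other branch is miscalibrated under the plan's own SDs.** If Levene happens not to reject, every pairwise comparison uses one pooled variance, which is too small for some pairs and too large for others.

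At stake are the clarity of the primary estimand and the calibration of the ALA versus vitamin E contrasts. The validity of the whole trial is not at stake.

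**Working it through.** **Inputs** (sample size section {14}): mean changes 12.05, 6.56, 4.15, 1.42; SDs 3.96, 8.90, 8.68, 7.60; alpha 0.05; power 80%; 16 per group, raised to 20. Assumed for the simulations: normal data, equal group sizes, mean-centred Levene at 5%, Shapiro-Wilk not modelled.

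**1. The plan's own figure.** The grand mean is 24.18/4 = 6.045. The squared deviations sum to 36.06 + 0.27 + 3.59 + 21.39 = 61.31. For one-way ANOVA the noncentrality is n × 61.31/SD².

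- Common SD 8.90, n = 16: 16 × 61.31/79.21 = 12.4, power 82.6%. At n = 15 power is 79.7%. The stated 16 is reproduced.
- Root-mean-square SD √((15.68 + 79.21 + 75.34 + 57.76)/4) = 7.55: n = 12 suffices (power 83.4%).
- Dropout: 16/0.80 = 20.

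So 16 is consistent with using the largest SD for all groups. That is conservative, but it sets aside the unequal SDs listed beside it.

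**2. Heterogeneity in the planning values.** (8.90/3.96)² = 5.05. Without the value 3.96 it is (8.90/7.60)² = 1.37.

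**3. How often Levene rejects at these SDs.** About 67% of trials at n = 16 and 80% at n = 20. The remaining 33% and 20% go to ANOVA although the variances differ. Even with normal data and equal SDs the choice would vary: if Shapiro-Wilk were run in each of four groups (an assumption) alongside Levene, each at 5% and treated as independent, 1 − 0.95⁵ = 22.6% of trials would go to the rank branch.

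**4. Pairwise standard errors on the ANOVA branch, n = 16.** Pooled: 7.55 × √(2/16) = 2.67 for every pair. True: √((SD₁² + SD₂²)/16).

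| Pair | True SE | Pooled SE |
|---|---|---|
| Surgical ALA vs surgical vitamin E | 2.44 | 2.67 |
| Non-surgical ALA vs non-surgical vitamin E | 2.88 | 2.67 |
| Surgical vitamin E vs non-surgical ALA | 3.11 | 2.67 |
| Surgical ALA vs non-surgical vitamin E | 2.14 | 2.67 |

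**5. Error of those comparisons.** With six pairs the Bonferroni level is 0.05/6 = 0.83%. In simulations with equal means, limited to trials where Levene passed and the overall test was significant, per-pair error runs from about 0.1% (surgical ALA vs non-surgical vitamin E) to 2.6% (surgical vitamin E vs non-surgical ALA). For non-surgical ALA vs vitamin E it is about 1.6%.

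**6. Power for the surgical ALA vs vitamin E contrast.** At the planning means, n = 16 and the 0.83% level, the pooled comparison has about 24% power and a Welch comparison about 28%.

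**7. The rule as a whole.**

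| Quantity | Result |
|---|---|
| Omnibus type I error, Levene then ANOVA or Kruskal-Wallis | 5.2% (n = 16); 5.2–5.5% across runs (n = 20) |
| Omnibus type I error, Welch ANOVA throughout | 5.0–5.1% |
| Any false pairwise claim, ANOVA branch | about 4.5–4.8%; 5.4–5.9% given Levene passes |
| Four-group power, n = 16 | 98% (two-stage) vs 99.7% (Welch) |

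**The case against.** The strongest reply is that the rule does little numerical harm. This stands. Bonferroni correction behind a significant overall test keeps the family-wise error close to 5%, and four-group power is ample on either branch.

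Several stronger readings are tempting, and the documents do not support them:

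- **Pairwise type I errors of 7% to 9%.** Some pairs do reach 6.8% and 9.2% with the pooled SE at n = 16, but only in unadjusted 5% tests. The plan does not use such tests.
- **A badly inflated Kruskal-Wallis test.** With normal data and equal groups its error is about 5.2–5.5%. It rises to 6.6% with an assumed 20/12/16/16 split of completers, and to 8.8–9.9% with assumed gamma-skewed data and equal means. The article states neither condition, and Welch itself reaches 6.4–6.7% in the skewed case.
- **A weak pre-test.** Rejection in 67–80% of trials is moderate to conventional power. The objection is to choosing the estimand by a pre-test, whatever its power.
- **Unequal variance as an established fact.** The ratio of 5.05 depends on one SD, and the article does not show how many patients lie behind it. The other three SDs are close.

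It is also fair that Kruskal-Wallis remains a valid test of identical distributions and that the plan allows medians with quartiles as summaries. That does not supply a mean difference in PR. Nor can the matter be left to an unseen analysis plan, because the article states the rule explicitly.

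**Conclusion.** The point holds in a limited form and is worth correcting. The analysis section sends unequal-variance data to a test that does not address unequal variance and does not estimate the quantity behind the sample size. Under the plan's own SDs this is the likelier branch. On the other branch the pairwise comparisons err in both directions, and the surgical ALA versus vitamin E contrast loses about four percentage points of power at 16 per group.

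The size is modest: near-nominal omnibus and family-wise error, and a difference of under two percentage points in four-group power. The main cost is a primary test and estimand that are not fixed in advance. The figures rest on normal data, equal groups and the planning SDs; if the value 3.96 is atypical, heterogeneity is much weaker and the miscalibration shrinks. The argument about an estimand chosen by the data does not depend on that value.

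**What to change.** For the primary outcome, pre-specify one mean-based analysis that allows unequal variances and use it whatever Shapiro-Wilk or Levene shows. Welch ANOVA with Games-Howell comparisons is one option; a model with heteroscedasticity-consistent standard errors is another. Report mean differences in PR points with confidence intervals. Keep Kruskal-Wallis as a sensitivity analysis and the two pre-tests as description only.

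The cost is a change of wording and a slight loss of efficiency if the variances prove equal. No extra patients are needed for the four-group test: at the planning means and SDs, Welch ANOVA has 99.7% power with 16 per group and already about 84% with 8.

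### The non-parametric branch names a paired test (Wilcoxon signed-rank) for post-hoc comparisons between independent randomised groups, so those pairwise p-values would rest on an arbitrary pairing of men

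*Protocol article*

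**What the plan says.** All of the analysis wording is in the protocol article under Statistical methods for primary and secondary outcomes {20a}. Shapiro-Wilk and Levene tests decide the route. Data that pass both go to one-way ANOVA with Bonferroni-corrected comparisons. The rule for the rest reads: "Continuous data that do not obey normal distribution or have unequal variance will be analyzed with the Kruskal-Wallis test". For the pairwise step that follows it, the article prescribes this: "if the result is statistically significant, then the Wilcoxon signed-rank test, with a Holm-Bonferroni method correction for multiple comparisons". A later sentence gives the same signed-rank test to before-after comparisons within a group when data are not normal.

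Trial design {8} and Sequence generation {16a} describe four groups allocated 1:1:1:1, each man in one group only. Outcomes {12} makes the between-group comparison of change in semen parameters, mainly PR, the primary outcome.

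Sample size {14} treats the trial as a one-way comparison of four independent means. Its planning values for change in PR start with ALA after surgery: "changes in PR sperm mean value in the surgical observation group was 12.05, and the standard deviation was 3.96". The other three arms, as mean (SD), are 6.56 (8.90) for vitamin E after surgery, 4.15 (8.68) for ALA alone and 1.42 (7.60) for vitamin E alone.

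**The concern.** A signed-rank test works on the differences within pairs. For before-after data the pair is the man himself. Between two randomised groups there is no such pair, and no section of the article defines a matching. Run literally, the test would pair men by their position in the data file. A different but equally legitimate ordering would give a different p-value from the same data, and with unequal group sizes some men would have no partner.

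The comparisons at stake are those the trial is for. The objectives ask how ALA compares with vitamin E, with and without surgery; after a significant four-group test, only the pairwise step answers that. The planning SDs also make this branch a likely route for PR rather than a remote contingency.

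**Working it through.** **1. The plan's own sample size.** Inputs from Sample size {14}: "type I error *α* = 0.05 and the type II error *β* = 0.20 with 80% test power", plus the four means and SDs above.
- Mean of the four means: (12.05 + 6.56 + 4.15 + 1.42)/4 = 6.045.
- Deviations: 6.005, 0.515, −1.895, −4.625. Sum of squares: 36.06 + 0.27 + 3.59 + 21.39 = 61.31.
- One-way ANOVA noncentrality: n × 61.31/SD². With the largest SD as common SD and n = 16: 16 × 61.31/8.90² = 12.38, giving power 0.826; 16 is the smallest n that reaches 0.80.
- Dropout: 16/(1 − 0.20) = 20 per group.

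The stated 16 and 20 are reproduced. The article does not say which common SD was used. The root-mean-square SD (7.55) would give 12 and the average SD (7.285) would give 11. The size rests on the omnibus test, so this point leaves it unchanged.

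**2. How often PR enters the branch.** The largest-to-smallest SD ratio is 8.90/3.96 = 2.25, a variance ratio of 5.05. Ten thousand trials per n were simulated from normal data with the planning means and SDs, each pre-test at 0.05 (assumed; the article gives no separate level for them).

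| | n = 16 | n = 20 |
|---|---|---|
| Levene rejects, mean-centred | 67% | 80% |
| Levene rejects, median-centred | 54% | 72% |
| Branch entered, mean-centred Levene or Shapiro-Wilk in any group | 74% | 84% |
| Branch entered, median-centred Levene or Shapiro-Wilk in any group | 64% | 78% |
| Kruskal-Wallis significant | 98% | 99.8% |
| Branch entered (mean-centred) and Kruskal-Wallis significant | 73% | 84% |

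Repeat runs move these by about a percentage point, hence a range of about 64–85%.

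Sensitivity to the SD of 3.96 (mean-centred Levene, Shapiro-Wilk per group, the range covering both n): if it were 5, 50–57%; if 6, 37–39%; with all four SDs equal, 22–24%.

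**3. How far the p-value moves with the pairing.** Two samples of 20 normal scores were given the planned surgical-arm means and SDs (12.05/3.96 and 6.56/8.90). The unadjusted rank-sum p is 0.02 (0.019 to 0.021, depending on how the scores are scaled). The signed-rank p over thousands of random pairings of the same 40 values has a median of 0.024. Its central 95% runs from 0.006 to between 0.058 and 0.064, depending on the run. The extremes were about 0.001 and 0.11 in one run; the upper one is unstable and was 0.13 in another.

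Holm sharpens this. Four groups give 4 × 3/2 = 6 pairs. If this comparison ranked third smallest, as its planned mean difference (12.05 − 6.56 = 5.49) ranks third largest, its Holm threshold would be 0.05/4 = 0.0125. The rank-sum p of 0.02 misses that; the signed-rank p can fall on either side.

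**4. Average behaviour.** Per-comparison power at unadjusted 0.05 (4,000 simulations), rank-sum against arbitrarily paired signed-rank:
- Surgical ALA versus vitamin E: 0.55 against 0.52 (n = 16), 0.66 against 0.66 (n = 20).
- Non-surgical ALA versus vitamin E: 0.13 against 0.12 (n = 16), 0.18 against 0.18 (n = 20).

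The two tests reach different verdicts in 11% of surgical and 6–8% of non-surgical comparisons. With equal means and SDs of 3.96 and 8.90, the type I error of the arbitrarily paired signed-rank test is 0.043–0.051, and that of rank-sum 0.057–0.062.

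**The case against.** The kindest reading is that signed-rank is a slip for rank-sum. The separate sentence on within-group data shows that the authors distinguish paired from unpaired comparisons. That is plausible, but the same name stands correctly in the next sentence and no other section corrects its use here, so an analyst following the text would run the wrong test.

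Several stronger readings are tempting, and the documents do not support them.

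- *The primary between-group p-value depends on row order.* Only the post-hoc pairwise p-values do. The first between-group test in this branch is Kruskal-Wallis, which ignores row order.
- *The trial would produce false positives.* Pairing made without regard to outcome keeps type I error near 0.05, and about 93% of pairings in the surgical example agree with rank-sum at an unadjusted 0.05. Far smaller p-values can be manufactured by sorting each arm by outcome before pairing, but nothing in the article suggests that.
- *The result could not be reproduced.* The same file in the same order returns the same p-value. The fault is that the order carries no meaning.
- *Many men would be discarded.* The missing-data section ({20c}) prescribes intention-to-treat with last record carried forward, which would hold the groups near 20 each. Unpaired men remain possible but need not be many.
- *Unequal planning SDs alone make the branch likely.* This is fragile. The only earlier semen record is baseline, so carrying it forward means zero change. With 4 of 20 men per arm set to zero, a simulation still entered the branch in about 75–77% of trials, but Levene rejected in only 9–18%; Shapiro-Wilk did the work. Entry most of the time survives; the reason shifts.

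It is also fair to say that choosing the test by pre-tests is common and here fixed in advance. Whether to replace that rule is a separate design choice.

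**Conclusion.** The error stands as a wrong test named for the post-hoc step. Individual pairwise results, including ALA versus vitamin E on PR, would rest on an arbitrary pairing; the omnibus test, the sample size and average error rates would not be harmed. The step is a likely one for PR, but the 64–85% assumes normal data and pre-tests at 0.05, and it falls to 22–24% if the four SDs are equal. The p-value spread comes from one constructed dataset without multiplicity adjustment; it illustrates the dependence and does not predict the trial's result. The test is invalid for these comparisons however often the branch is reached, so the wording should be corrected before analysis.

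**What to change.** In {20a}, replace the signed-rank test after Kruskal-Wallis by the Wilcoxon rank-sum (Mann-Whitney) test, or by Dunn's test, with the Holm correction kept. State that signed-rank is used only for before-after data within a group. This costs one sentence of wording; sample size, data collection and the rest of the analysis are unchanged.

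Optionally, and as a separate improvement, fix the PR analysis in advance as a comparison of mean changes that is valid under unequal variances (such as Welch) instead of letting pre-tests choose between means and ranks. That would match the means on which the trial was sized and costs another sentence or two.

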### Interim analyses {21b}

No interim analyses will be performed.

### Methods for additional analyses (e.g., subgroup analyses) {20b}

No subgroup analyses are planned.

### Methods in analysis to handle protocol non-adherence and any statistical methods to handle missing data {20c}

When analyzing the results, we will conduct an intention-to-treat analysis for missing data. The last record data will be carried over to the end, and if a large number of missing data are found in further statistical analysis, multiple interpolation will be considered.

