#### Strategies to improve adherence to interventions {11c}

Monthly follow-up and record adverse drug reactions. Research participants can contact the investigators by phone or WeChat at any time, feed back drug use and treatment, and obtain guidance or suggestions.

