### Outcomes {12}

The primary outcome is the change of semen parameters (mainly progressive motility sperm) compared between the study groups at baseline and after 3 months of oral medication. Semen samples will be collected in sterile containers by masturbation after 2–7 days of abstinence. A semen analysis will be performed within 60 min after ejaculation and liquefaction using semen quality analyzer, and the semen volume, PH, sperm concentration, total motion, progressive motility (PR), and normal morphology will be measured according to the WHO laboratory manual for the examination and processing of human semen (5th edition) [25].

As secondary outcomes, the following will be measured at baseline and after 3 months of treatment: (1) Sex hormones, including follicle-stimulating hormone (FSH), luteinizing hormone (LH), estradiol (E2), and testosterone (T), will be determined by electrochemiluminescence using fasting blood. (2) Testicular volume will be calculated using Lambert’s formula (length × height × width × 0.71) [26]. (3) Sperm DNA fragment index (DFI) will be detected by flow cytometry-assisted sperm chromatin structure analysis (SCSA), seminal plasma malondialdehyde (MDA) levels will be detected by means of the tiobarbituric acid method, and seminal plasma total antioxidant capacity (TAC) will be detected by ferric-reducing antioxidant power (FRAP) assay method. (4) The pregnancy rate will be assessed during the 6-month follow-up after the completion of the trial.

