### Data collection and management

#### Plans for assessment and collection of outcomes {18a}

Data will be collected at three time points: (T0) pre-treatment (baseline) records—baseline parameters, sperm quality, sex hormones, testicular volume, sperm DFI, seminal plasma MDA, and TAC; (T2) 3 months post-treatment—sperm quality, sex hormones, testicular volume, DFI, seminal plasma MDA and TAC, and adverse event; and (T3) 6 months post-treatment—pregnancy rate.

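### With only one semen sample after baseline, carrying the last record forward scores every man who misses it as exactly zero change

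*Protocol article*

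**What the plan says.** The primary outcome (Outcomes {12}) is a change score: "The primary outcome is the change of semen parameters (mainly progressive motility sperm) compared between the study groups at baseline and after 3 months" of medication. Section {18a} states "Data will be collected at three time points". Baseline (T0) covers all the laboratory and ultrasound measures. The next entry is "T2) 3 months post-treatment—sperm quality, sex hormones, testicular volume, DFI, seminal plasma MDA and TAC, and adverse event". The last is "T3) 6 months post-treatment—pregnancy rate", with no semen sample. Between visits, section {11c} provides for "Monthly follow-up and record adverse drug reactions", again without a sample.

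Section {20c} labels its approach to missing data intention-to-treat and gives the default: "The last record data will be carried over to the end". It then adds that "if a large number of missing data are found in further statistical analysis, multiple interpolation will be considered". No threshold for a large number is given.

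The Sample size section {14} "estimated a dropout rate of 20"% and goes from 16 to 20 men per group on that basis.

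**The concern.** Carrying a value forward presupposes an intermediate value to carry. Here there is none: for the primary outcome and every continuous secondary outcome, the last record of a man who misses the 3-month visit is his baseline. The rule therefore enters a change of zero and treats it as observed.

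Three things follow. Arms expected to improve most are pulled down most. Any imbalance in dropout becomes a difference between arms. And the sample size was built so that 16 observed men per arm remain, whereas the analysis would use 20, about 4 of them set to zero.

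**Working it through.** **Inputs** (Sample size {14}). Planned PR change, mean (SD): surgical ALA 12.05 (3.96); surgical vitamin E 6.56 (8.90); non-surgical ALA 4.15 (8.68); non-surgical vitamin E 1.42 (7.60). Alpha 0.05, power 80%, 16 per group, 20% dropout, 20 per group.

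**1. Reproducing the plan's figure.** The grand mean is (12.05 + 6.56 + 4.15 + 1.42)/4 = 6.045. The squared deviations sum to 36.06 + 0.27 + 3.59 + 21.39 = 61.31. With a common SD of 8.90 and n = 16, the noncentrality is 16 × 61.31/8.90² = 12.38. The noncentral F with 3 and 60 degrees of freedom then gives power 0.826, and 16 is the smallest n reaching 80%. The protocol does not state its common SD; 8.90, the largest of the four, is inferred because it gives 16. The root-mean-square SD of 7.55 would give 12. Dropout: 16/(1 − 0.20) = 20, as stated.

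**2. The imputed value.** With no 3-month sample, change = T0 − T0 = 0.

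**3. Equal dropout d = 0.20, unrelated to outcome.** Expected mean = (1 − d) × planned mean.

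| Arm or difference | Planned | After the rule |
|---|---|---|
| Surgical ALA | 12.05 | 9.64 |
| Surgical vitamin E | 6.56 | 5.25 |
| Non-surgical ALA | 4.15 | 3.32 |
| Non-surgical vitamin E | 1.42 | 1.14 |
| Surgical ALA − vitamin E | 5.49 | 4.39 |
| Non-surgical ALA − vitamin E | 2.73 | 2.18 |

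SD = √[(1 − d)SD² + d(1 − d)mean²]. For surgical ALA: √(0.8 × 3.96² + 0.16 × 12.05²) = √(12.55 + 23.23) = 5.98, against 3.96 planned.

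**4. Power** (simulation; exactly 4 of 20 lost per arm; observed cases against carried-forward zeros).

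| Test | SD assumption | Observed cases | After the rule |
|---|---|---|---|
| Overall F test | 8.90 in all arms | about 83% | 78–79% |
| Overall F test | each arm's own | about 97% | about 95% |
| Surgical pair, unadjusted | 8.90 in all arms | about 39% | about 31% |
| Surgical pair, unadjusted | each arm's own | about 59% | about 45% |

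**5. Unequal dropout** (rates assumed; the protocol gives none by arm). Expected difference = (1 − d₁) × mean₁ − (1 − d₂) × mean₂.

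- ALA loses 30%, vitamin E 10%: the surgical difference is 0.7 × 12.05 − 0.9 × 6.56 = 2.53, against a true 5.49. Overall power at SD 8.90 is about 64%.
- ALA loses 10%, vitamin E 30%: 0.9 × 12.05 − 0.7 × 6.56 = 6.25, above the true value.
- No true difference (every arm changes by 6.0, SD 8; assumed), 10% against 30% by drug: a false difference of 6.0 × (0.9 − 0.7) = 1.2 points, and an overall type I error of about 6%.
- Same null, 10% lost in both surgical arms and 30% in both non-surgical arms: 1.2 points between surgical and non-surgical arms, and 6.0 × (0.9 − 0.9) = 0 between ALA and vitamin E within the surgical pair (likewise 0 in the non-surgical pair).
- Same null, exactly 20% lost in every arm: the overall test rejects in about 3%, so it is conservative. This depends on fixing the number lost in each arm; when I let that number vary by chance, the rate returned to about its nominal level.

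**The case against.** **The planned test barely suffers.** The trial is sized and analysed by a four-group comparison, with pairwise tests only after a significant overall result and with Bonferroni correction. A reader might infer from the pairwise figures that the rule badly weakens the primary analysis. The documents do not support that: at the planned dropout the F test loses 2 to 5 points. The pairwise powers are low mainly for reasons unrelated to missing data. This stands and limits the severity.

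**False ALA effects need unequal loss by drug.** Section {17a} says participants cannot be blinded to surgery, which makes different dropout between surgical and non-surgical arms plausible. A reader might infer a spurious ALA effect from that. It does not follow: equal loss within each surgical stratum leaves a null ALA comparison at zero. What is distorted is surgical against non-surgical, which does belong to the specific objective. Larger false differences can be built, for example 12.05 × (0.9 − 0.7) = 2.41 points, but that needs two arms that both change by 12.05 and loss rates that the protocol does not give.

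**The details may sit elsewhere.** A separate analysis plan may define the imputation trigger and model, so the missing threshold is secondary. The default itself, however, is stated here. Section {18a} skips the label T1 and Figure 2 is not shown, but the text counts three time points and places semen at only two of them.

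**Stopping the capsules is not dropping out.** Section {11b} stops the intervention, not follow-up. A man who stops but gives the 3-month sample is unaffected, so the 20% matters only as far as it means missing samples.

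**Conclusion.** The point holds, as a should-fix. That the rule yields zero change follows directly from sections {12}, {18a} and {20c}. Its size rests on 20% missing 3-month samples, loss unrelated to outcome, and the planned means: differences shrink by a fifth, the overall test loses little (though it slips just under the planned 80% with the SD that reproduces 16 per group), and the surgical pair loses 8 to 14 points.

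The rule cannot be defended as reliably conservative, because with unequal loss the bias can take either sign. Nor do the documents show that it generally inflates false positives: under equal loss it does not, and under the assumed 10% against 30% the excess is about one point. The fallback does not answer the concern, because it commits to nothing and leaves the choice of method until the data have been examined.

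**What to change.** In section {20c}, delete last-record-carried-forward. Name in advance, whatever the amount missing, one primary analysis of men in the groups to which they were randomised, valid under missing at random. Either of these would serve:

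- ANCOVA on observed 3-month PR with baseline PR as covariate; or
- multiple imputation with a small model pooled across arms: arm, baseline PR and at most one or two other baseline measures. Imputing separately by arm from the full set of semen and oxidative-stress measures would put about nine predictors on some 16 observed men and would overfit.

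Add one delta-adjusted sensitivity analysis in which the imputed changes are shifted, by arm, until the conclusion changes.

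The cost is a few lines of text and a little more analysis work. ANCOVA would also mean aligning the primary test in section {20a}. Both options rely on missing at random, which the data cannot verify; the sensitivity analysis probes it.
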